### Assessment of EA safety

Acupuncture is considered to be a generally safe procedure [15]; however, all adverse events will be recorded in detail. In this study, EA-related adverse events would mainly refer to broken needles, fainting due to the needling procedure, continuous post-needling pain lasting >2 h, local infection, hematoma, bleeding, and other events that can be caused by acupuncture (such as fatigue, headache, insomnia, and dizziness).

### Assessment of the subject blinding success rate

Two of the study centers will be randomly selected to measure the success rate of subject blinding via analyzing questionnaire response (Figure 2). The questionnaire will be completed by subjects within 5 min after any treatment session in weeks 3 and 6. The percentage of subjects from each group who believe that they received a true EA treatment (regardless of whether they received an actual true or actual sham treatment) will be recorded as P1 in week 3 and P2 in week 6. The subject blinding success rate will be defined as the average of P1 and P2. The difference in the subject blinding success rates between the two groups will be analyzed.

**Figure 2 F2:**
[figure not shown]
Blind method assessment questionnaire.

### Statistical methods

#### Sample size calculation

We conducted a pilot study comparing the effects of deep EA with shallow EA on women with SUI in Guang’an men Hospital of CACMS between June 2011 and February 2012. Results from our pilot study revealed that: compared with the baseline, the volume of urine leakage from the 1-h pad test decreased by 2.10 g, with a standard deviation of 2.26, after 4 weeks deep EA treatment, and by 0.64 g with a standard deviation of 0.97 after 4 weeks shallow EA treatment [16]. We performed sample size calculation according to results of our pilot study because no placebo control trial has been reported. A sample size of 117 in each group will be sufficient to detect a clinically important difference of 1 g on the volume of urine leakage from a 1-h pad test, assuming a standard deviation of 2.61 (considering a larger variability in multicenter trial, the pooled standard deviation of pilot study 1.74 was expanded by 1.5 times), using a one-tailed *t*-test of the difference between means, a significance level of 5%, and a power of 90%. The calculation is based on the assumption that measurements on volume of urine leakage from a 1-h pad test are normally distributed. This number has been increased to 140 per group (total of 280), to allow for a predicted drop-out rate of 20%. As our pilot study had a small sample size (*n*=40) and as we will undertake subgroup analysis, we expanded the sample size to 500 cases (250 cases in each group) to enhance the reliability of the study.

#### Statistical analysis

Statistical analysis will be performed by the Clinical Evaluation Center of CACMS in Beijing and the Department of Biostatistics, University of Washington, Seattle, United States. The statistician will be blinded from the allocation of groups. PASW Statistics 20.0 and SAS9.0 statistical software will be used for data analysis. The level of significance is established at α<0.05 with a two-tailed test.

The main objective is to compare the change in the amount of urine leakage at week 6 from the baseline between the treatment group and the control group. The null hypothesis is that the treatment group has the same change as the control group, while the alternative hypothesis is that the treatment group shows a greater decrease.

Continuous data will be represented by the average, standard deviation, median, minimum value, and maximum value, whereas categorical data will be represented by percentages. For comparison with the baseline, a *t*-test or non-parametric test will be used for continuous data, and non-parametric tests for categorical data. For comparison of two independent samples: if the residual are normally distributed, the analysis of covariance (ANCOVA) will be used for the primary outcome and subgroup analysis stratified by incontinence severity, a *t*-test for other continuous data, and a chi-square test for categorical data; if the residual are abnormally distributed, a non-parametric test will be used for both continuous and categorical date. Detailed contents and methods are as follows.

1. Case distribution and compliance analysis: The case distribution of both groups in every center will be described. The total drop-out rate and the drop-out rate due to adverse events, of both groups, will be compared using Fisher’s exact test.

2. Analysis of baseline characteristics.

3. Analysis of compliance: The implementation of protocol intervention will be compared between the two groups. Compliance will be evaluated according to the case report forms.

4. Analysis of efficiency: Intention-to-treat (ITT) analysis will be used to assess the validity of the study. Efficiency analysis will be based on the ITT population which is defined as all randomized participants. Missing data and non-compliance data will be included in the efficiency analysis. Missing data, from subjects without any treatment after randomization, or without any valid data of evaluation although treated, will be analyzed by multiple imputation by the inverse probability weighting method. Non-compliance data will be analyzed by the instrumental variable.

5. Analysis of primary outcome: In this study, we will use the change in the amount of urine leakage at week 6 from the baseline as the primary outcome. To adjust for baseline imbalance, a comparison of the decreased value of urine leakage between the groups will be done by ANCOVA using baseline and centers as covariates, when the residual are normally distributed. Meanwhile, a covariance model including interactions between centers and group will be made to analyze the center effect. Causes will be further analyzed if any center effect is identified. Comparison of decreased value of urine leakage between groups will be analyzed by a non-parametric test if the residual are abnormally distributed with neglect of baseline balance.

6. Analysis of secondary outcomes:

A 72-h incontinence episode frequency (IEF), the International Consultation on Incontinence Questionnaire-Urinary Incontinence (ICIQ-UI) Short Form score, and weekly consumption of pads of weeks 6, 18, and 30 will be compared with their respective baselines, and a *t*-test or non-parametric test will be used for comparison among groups.

For severity of urinary incontinence based on a 72-h bladder diary and a self-report assessment of therapeutic effect, the case number and percentage of each rank of weeks 6, 18, and 30 will be compared with their baselines, and a chi-square test or non-parametric test will be used for comparison among groups.

Although we will exclude patients already receiving some form of treatment for SUI at the trial outset and will discourage participants from taking additional treatments during the trial period, we anticipate that some patients will not adhere to this. In these instances the patients will record the treatments received and/or medications taken and the number of patients and treatment sessions of the treatment period and two follow-up periods will be described, and chi-square tests or non-parametric tests will be used for comparison among groups.

To assess the effect of EA for different degrees of SUI, subgroup analysis will be stratified by incontinence severity measured by a 1-h pad test at the baseline. In comparison among the groups, changes in the amount of urine leakage at week 6 from the baseline will be analyzed by ANCOVA or nonparametric tests. Changes in the 72-h IEF at weeks 18 and 30 will be analyzed by covariance analysis, non-parametric tests, or longitudinal data model.

7. Analysis of safety: Adverse events will be listed and analyzed using a chi-square test or Fisher’s exact test. Severe adverse events should be listed in detail. EA-related adverse events are to be listed in detail and compared among groups.

8. Analysis of blind method: The number and percentage of subjects choosing true EA in the selected two centers will be established. A chi-square test or non-parametric test will be used for comparison among groups.

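### The sample size is computed for a one-tailed 5% test although the declared analysis is two-tailed at 5%, and the 20% drop-out allowance is under-inflated; the printed 117 and 140 per group do not support 90% power for that analysis, though the planned 250 per group does

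*Protocol article*

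**What the plan says.** The target in the Sample size calculation section is "a clinically important difference of 1 g on the volume of urine leakage from a 1-h pad test". For the variability, the section proceeds by "assuming a standard deviation of 2.61" and explains that "the pooled standard deviation of pilot study 1.74 was expanded by 1.5 times". The calculation is made "using a one-tailed *t*-test of the difference between means, a significance level of 5%, and a power of 90" per cent, and the result is reported as "A sample size of 117 in each group will be sufficient to detect" that difference. For losses it adds: "This number has been increased to 140 per group (total of 280), to allow for a predicted drop-out rate of 20" per cent. The section then raises the target to 250 per group (500 in all), giving the small pilot and the planned subgroup analysis as reasons. It states no power for 250 per group.

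The Statistical analysis section says "The level of significance is established at α<0.05 with a two-tailed test" and makes no exception for the primary outcome. Its next paragraph sets a null of equal change in the two groups and says "the alternative hypothesis is that the treatment group shows a greater decrease".

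**The concern.** A one-tailed 5% test allows a 5% chance of a false claim of benefit; a two-tailed 5% test allows 2.5% in that direction. A sample size computed for the former is too small for the same power under the latter. The one-tailed calculation and the directional alternative agree with each other, and the two-tailed level differs from both. The printed 90% power therefore belongs to a test that the analysis section does not adopt.

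The drop-out step is a separate slip. If a fraction d is lost, the number to randomise is n/(1 − d), not n(1 + d). The second form leaves the trial short of n whenever d is above zero.

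At stake is whether a reader can rely on the stated power. The reader also cannot tell how much of the step from 140 to 250 is real margin and how much makes good these two slips.

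**Working it through.** **Inputs**, all from Sample size calculation unless noted: difference 1 g; SD 2.61; power 90%; one-tailed 5% for sizing; drop-out 20%; 117, 140 and 250 per group. The two-tailed 5% level is from Statistical analysis, and 1:1 allocation is from Study design.

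**1. The SD.** With equal groups, the pilot SDs of 2.26 and 0.97 pool to √((2.26² + 0.97²)/2) = 1.739. The article's 1.74 × 1.5 = 2.61. This reproduces.

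**2. The plan's 117.** n per group = 2·SD²·(z_α + z_β)²/δ².
- One-tailed 5%: 2 × 2.61² × (1.645 + 1.282)² = 116.7, so 117. This reproduces (exact t gives 118).
- Two-tailed 5%: 2 × 2.61² × (1.960 + 1.282)² = 143.2, so 144 (exact t gives 145).

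**3. The drop-out step.**
- 117 × 1.2 = 140.4, which is the printed 140.
- 140 × 0.8 = 112 evaluable, 5 fewer than 117.
- 117/0.8 = 146.25, so 147 per group (294 in total) if the one-tailed basis were kept.
- 144/0.8 = 180 per group (360 in total) for the two-tailed test. From 145: 181.25, so 182 (364 in total).

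**4. Power at each size.** By the normal approximation, power = Φ(δ/(SD·√(2/n)) − z_crit). For n = 117 the first term is 1/(2.61 × √(2/117)) = 2.93. Two-tailed power is Φ(2.93 − 1.96) = 83.4% and one-tailed power is Φ(2.93 − 1.645) = 90.1%. In the table, the normal approximation comes first and the noncentral t second.

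| Evaluable per group | How it arises | One-tailed 5% | Two-tailed 5% |
|---|---|---|---|
| 112 | 140 less 20% | 88.9% / 88.8% | 81.8% / 81.5% |
| 117 | stated requirement | 90.1% / 89.9% | 83.4% / 83.1% |
| 140 | 140, no loss | 94.1% / 94.0% | 89.4% / 89.2% |
| 200 | 250 less 20% | 98.6% / 98.5% | 96.9% / 96.9% |
| 250 | 250, no loss | 99.6% / 99.6% | 99.0% / 99.0% |

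**5. Which slip matters more.** At 117, the change from one-tailed to two-tailed costs 90.1 − 83.4 = 6.7 points. On the one-tailed basis, the drop-out slip costs 90.1 − 88.9 = 1.2 points. Sidedness causes most of the shortfall.

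**6. Margin at the planned size.** With 200 evaluable per group, two-tailed power stays at 90% or more up to an SD of 1/(√(2/200) × (1.960 + 1.282)) = 3.08, compared with the assumed 2.61.

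**The case against.** The strongest reply is that 117 and 140 are intermediate figures. The trial will recruit 250 per group, which after 20% loss exceeds both 117 and the corrected 144 to 145. That stands, and it limits the consequence. It does not make the printed figures right. The article justifies 250 by the small pilot and the subgroup analysis, not by a two-tailed calculation, and the true margin is 250 against 180 to 182, not 250 against 140.

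Three stronger readings are tempting, and the documents support none of them.

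- *The trial is underpowered.* It is not, on its own assumptions: two-tailed power is about 97% with 200 evaluable per group.
- *The 117 is miscalculated.* It is not. It reproduces for the one-tailed test named beside it, and falls short only under the two-tailed level of the analysis section.
- *The decision rule is open, so a one-sided p between 0.025 and 0.05 could be called either way.* The analysis section states a two-tailed 5% level, under which such a result is not significant. A sizing assumption does not set the rule for declaring significance, and the directional alternative names no second level. Its wording is loose and should be aligned.

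A further fair point is that the planned primary analysis is ANCOVA on baseline and centre in all randomised participants, with missing data imputed, and a non-parametric test if residuals are not normal. The power figures here use the article's own unadjusted t-test. No baseline correlation is given, so any effect of adjustment cannot be quantified.

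**Conclusion.** The point holds as an inconsistency in the sample size justification, of minor to moderate weight. For the declared two-tailed 5% test, 117 per group gives about 83% power, and 140 randomised with 20% lost gives about 81.5%, not 90%. The correct requirement is 144 evaluable and 180 randomised per group (145 and 182 by exact t). The planned 500 remains adequate for the primary comparison. These results assume a true difference of 1 g, a common SD of 2.61, normally distributed changes, an unadjusted t-test and 20% loss in each group. They say nothing about power within the severity subgroups.

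**What to change.** - State one test in both sections: two-sided at 5%, with a two-sided alternative in place of the directional one. This keeps the level that the analysis section already declares. A one-tailed design with its level justified would also be consistent, but it would reverse that declaration and would still need 147 per group instead of 140.
- Replace 117, 140 and 280 by 144 evaluable and 180 randomised per group, 360 in total (145, 182 and 364 by exact t), with the allowance computed as n/(1 − 0.20).
- Report that 250 per group, with 200 evaluable, has about 97% two-sided power for 1 g at SD 2.61. Note that this assumes an unadjusted t-test and not the planned ANCOVA.

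The cost is a few restated figures and a reworded hypothesis. Enrolment stays at 500 and the analysis does not change. The article describes the trial as still recruiting, so the change can be made before any data are unblinded.

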## Methods

### Study design

This is a multicenter subject-blinded randomized controlled trial comparing EA with sham EA. Five hundred women with pure SUI will be recruited from the following 12 hospitals in China: Guang’an men Hospital of China Academy of Chinese Medical Sciences (CACMS); Xiyuan Hospital of CACMS; Dongzhimen Hospital affiliated to Beijing University of Chinese Medicine; Yueyang Hospital of Integrated Traditional Chinese and Western Medicine affiliated to Shanghai University of Traditional Chinese Medicine (TCM); West China Hospital of Sichuan University; First Teaching Hospital of Tianjin University of TCM; First Hospital of Hunan University of Chinese Medicine; Hengyang Hospital affiliated to Hunan University of Chinese Medicine; Hubei Provincial Hospital of TCM; Jiangsu Province Hospital of TCM;, Shanxi Province Hospital of TCM; and Shanxi Hospital of Integrated Traditional and Western Medicine. Participants will be randomly assigned (on a 1:1 ratio) to the EA group or the sham EA group by a central randomization system performed by the Clinical Evaluation Center of the CACMS in Beijing. The randomization sequence will be generated by the ‘proc plan’ procedure of the SAS9.3 analytic software according to center-stratified, block randomization with a block size of six. Random number and group assignment will be offered by telephone, mobile phone, or website from the Clinical Evaluation Center of the CACMS. In this study, participants, outcome assessors, and statisticians will be blinded to treatment allocation. The flowchart and study design schedule are presented in Figure 1 and Table 1, respectively.

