**Secondary outcomes**	
1. 72-h IEF	Evaluated at weeks 6, 18, and 30. The change of average 72-h IEF from the baseline will be analyzed
	Based on a 72-h bladder diary, the average 72-h IEF of week 6 is calculated by averaging the IEF of weeks 2, 4, and 6; values of week 18 and 30 are calculated by averaging IEF of weeks 15–18 and 27–30, respectively
2. ICIQ-UI Short Form score	Evaluated at weeks 6, 18, and 30. The change of score from the baseline will be analyzed
3. Severity of urinary incontinence	Evaluated at weeks 6, 18, and 30. Change in the number and percentage of severity rating from the baseline will be analyzed
	The most severe degree during weeks 2, 4, and 6 will be taken as severity of urinary incontinence of week 6
	The most severe degree during weeks 15–18 and weeks 27–30 will be taken as severity of urinary incontinence of week 18 and week 30, respectively
4. Self-report assessment of therapeutic effect	Evaluated at weeks 6, 18, and 30
	A 4-point scale is used: no help, little help, medium help, and great help
5. Weekly consumption of pads	Evaluated at weeks 6, 18, and 30. The change in average consumption of pads from the baseline will be analyzed
	The pads consumption of weeks 6, 18, and 30 will be calculated by averaging the weekly usage of pads during weeks 1–6, weeks 7–18, and weeks 19–30, respectively
6. Application of other treatment for SUI (including drugs and other specialist treatment)	Evaluated at weeks 6, 18, and 30. The number of patients who used other treatments for SUI during the trial will be analyzed between the two groups
7. Subgroup analysis stratified by incontinence severity	Evaluated at weeks 6, 18, and 30
	Stratified by incontinence severity at the baseline, the correlation between the rating of incontinence severity and the treatment effect will be analyzed. Different outcomes of treatment effect are used in each evaluation: week 6, the change in amount of urine leakage at week 6 from the baseline measured by 1-h pad test; week 18, the change of average 72-h IEF at week 18 from the baseline; and week 30, the change of average 72-h IEF at week 30 from the baseline

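### The overall comparisons of 72-h IEF, ICIQ-UI SF and weekly pads leave out baseline and centre as covariates, a loss of efficiency that can be recovered without new data

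*Protocol article*

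**What the plan says.** All references are to the Protocol article.

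- **General rule (Statistical analysis).** With normal residuals, "analysis of covariance (ANCOVA) will be used for the primary outcome and subgroup analysis stratified by incontinence severity, a *t*-test for other continuous data". Otherwise, "if the residual are abnormally distributed, a non-parametric test will be used for both continuous and categorical date".
- **Item 6, secondary outcomes.** IEF and ICIQ-UI SF are handled in the same sentence as pads: "weekly consumption of pads of weeks 6, 18, and 30 will be compared with their respective baselines". The method it then names for the two arms reads: "a *t*-test or non-parametric test will be used for comparison among groups". No covariate is named.
- **Scale of analysis (Table 2).** All three outcomes are changes from baseline. For IEF: "The change of average 72-h IEF from the baseline will be analyzed". For ICIQ-UI SF: "The change of score from the baseline will be analyzed". For pads: "The change in average consumption of pads from the baseline will be analyzed". Each is evaluated at weeks 6, 18 and 30.
- **Baseline data (Table 1).** The bladder diary, pad consumption and ICIQ-UI SF are all recorded at week 0.
- **Randomisation (Study design).** Twelve hospitals, 1:1, by "center-stratified, block randomization with a block size of six".
- **Primary outcome (Statistical analysis, item 5).** ANCOVA with baseline and centre when residuals are normal. The reason given is to deal with baseline imbalance.
- **Severity subgroup analysis (item 6, last paragraph).** For change in IEF at weeks 18 and 30, covariance analysis, a non-parametric test or a longitudinal model is allowed. No covariates are listed for it.

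**The concern.** The reason given for adjusting the primary outcome applies equally to the three continuous secondary outcomes, yet the article fixes an unadjusted method for them. The same variable, change in IEF at weeks 18 and 30, may be modelled with covariates within severity subgroups but not in the overall comparison.

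Precision is at stake. The 1-h pad test stops at week 6 (Table 1), so these three are the only continuous outcomes in Table 2 that compare the groups after treatment ends. A needlessly wide interval there makes it harder to say whether an effect lasts. Leaving out the stratification factor also means that the reported standard error does not match the design, although it errs on the cautious side.

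**Working it through.** **The plan's own figure.** The article states no power or precision for any secondary outcome. Its 117 per group concerns the pad test only. It reproduces (one-sided 5%, 90% power, SD 2.61 g, difference 1 g) but does not bear on this point.

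**Inputs from the article.** 250 per group; 20% drop-out, hence 250 × 0.8 = 200 evaluable per group; two-sided 5% test; 12 centres as strata.

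**Inputs assumed.** The correlation between baseline and follow-up (rho) and the intraclass correlation for centre (ICC). The article gives neither, so ranges are shown.

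**Step 1: baseline.** With a common SD s at baseline and follow-up:

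- variance of the change score = 2s²(1 − rho)
- residual variance under ANCOVA = s²(1 − rho²)
- change score relative to ANCOVA = 2(1 − rho)/(1 − rho²) = 2/(1 + rho)

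The number per group that would give ANCOVA the precision of the change-score test with 250 is 250(1 + rho)/2, or 200(1 + rho)/2 after drop-out. The last column takes an effect with 80% power under the change-score t-test (200 evaluable per group) and gives its power under ANCOVA, Φ[(1.960 + 0.842)/√((1 + rho)/2) − 1.960].

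| rho | variance ratio | ANCOVA equivalent of 250 | ANCOVA equivalent of 200 | 80% power becomes |
|---|---|---|---|---|
| 0.3 | 1.54 | 162.5 | 130 | 93.5% |
| 0.5 | 1.33 | 187.5 | 150 | 89.9% |
| 0.7 | 1.18 | 212.5 | 170 | 86.0% |
| 0.9 | 1.05 | 237.5 | 190 | 82.0% |

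**Step 2: unequal SDs.** Let k be follow-up SD divided by baseline SD. The ratio becomes 1 + (1 − rho·k)²/[k²(1 − rho²)], which is never below 1. IEF at follow-up averages three or four diaries (Table 2), while Table 1 shows one baseline diary, so k below 1 is plausible.

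- k = 0.8, rho = 0.5: 1 + 0.36/0.48 = 1.75
- k = 0.8, rho = 0.7: 1 + 0.1936/0.3264 = 1.59
- k = 1.2, rho = 0.5: 1 + 0.16/1.08 = 1.15

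**Step 3: chance imbalance.** With equal SDs, a fraction (1 − rho) of any chance difference at baseline passes into the change-score estimate, for example half of it at rho 0.5. ANCOVA removes this part.

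**Step 4: centre.** With near balance within centres, adjusted SE relative to unadjusted SE is about √(1 − ICC). The true type I error of the unadjusted test at nominal 5% is 2[1 − Φ(1.960/√(1 − ICC))].

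| ICC | SE falls by | true type I error |
|---|---|---|
| 0.01 | 0.5% | 4.9% |
| 0.02 | 1.0% | 4.8% |
| 0.05 | 2.5% | 4.4% |
| 0.10 | 5.1% | 3.9% |

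Steps 1 to 3 describe the t-test. The article's rank-test alternative also names no covariate, but these ratios do not measure its loss.

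**The case against.** The strongest defence is that nothing here is invalid. A two-sample test on change from baseline is sound under randomisation, leaving out centre makes it slightly conservative, and no precision target for a secondary outcome is missed because none is stated. That stands, and it limits the point to efficiency. It does not remove the gain: in large samples ANCOVA is never less precise than the change score.

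The size of the loss is also open to challenge. It depends on an assumed rho, and at 0.9 it is only 5% in variance. That stands too, which is why the whole range is given.

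A reader might infer more than the article supports:

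- *Baseline is ignored.* It is not. Table 2 defines the outcomes as changes, so the right comparison is change score against ANCOVA, as above.
- *Regression to the mean biases the result.* It is expected equally in both randomised groups and does not bias their difference. Only chance imbalance remains.
- *The whole follow-up claim rests on these tests.* Severity grade, self-reported effect and use of other treatments are also evaluated at weeks 18 and 30.
- *No adjusted or longitudinal model exists outside the primary outcome.* The severity subgroup analysis allows one. It does not cover the overall comparison.

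**Conclusion.** The point holds as a loss of efficiency in the overall comparisons of three secondary outcomes. It does not touch the primary conclusion, introduces no bias and does not inflate type I error.

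Under equal SDs the change-score t-test has 1.05 to 1.54 times the variance of ANCOVA for rho from 0.9 down to 0.3. The loss is moderate at low to middling correlations and small at high ones. The centre component is minor unless the ICC is large. Both ranges are assumptions; the wording of the planned tests is certain from the text, the size of the loss is not.

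**What to change.** In Statistical analysis, amend the general rule and item 6. Analyse the change in 72-h IEF, ICIQ-UI SF and weekly pads at weeks 6, 18 and 30 by ANCOVA with the baseline value of that outcome and centre as covariates, as in the primary model. If residuals are not normal, keep the model and use robust standard errors instead of moving to an unadjusted rank test. Report the adjusted difference between groups with its 95% CI at each time point.

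A longitudinal model for each outcome with the same covariates is an acceptable alternative, and the article already allows that type of model for IEF in the severity subgroup analysis. It is not required to cure this point.

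The change needs no new data, visits or patients. Because the trial is already recruiting (Trial status), it should be recorded as a dated amendment before unblinding and made consistent with the missing-data methods in item 4. It is a free improvement.

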### Outcome measures

The primary outcome will be the change in the amount of urine leakage at week 6 from the baseline, measured by a 1-h pad test. The change at week 2 from the baseline will also be assessed. The 1-h pad test will be conducted based on the International Continence Society (ICS) guidelines [14] at the baseline, at week 2, and at week 6 (see Table 2). Secondary outcomes include seven items, the details of which are listed in Table 2.

**Table 2 T2:** Trial outcomes

**Primary outcome**	**Time point**
Change in amount of urine leakage at week 6 from the baseline measured by 1-h pad test	Evaluated at week 6

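### Women who never start treatment are classed as missing data to be imputed, although the ITT population is all randomized women and the week-6 pad test is scheduled regardless of treatment

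*Protocol article*

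**What the plan says.** All the wording at issue is in the protocol article, mostly in item 4 (analysis of efficiency) of the statistical analysis section.

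- Population: "Efficiency analysis will be based on the ITT population which is defined as all randomized participants".
- What counts as missing: "Missing data, from subjects without any treatment after randomization, or without any valid data of evaluation although treated".
- How it is handled: these data "will be analyzed by multiple imputation by the inverse probability weighting method". The article does not give the imputation model, say whether it is fitted by arm, or state what is assumed about missingness.
- Non-compliance: "Missing data and non-compliance data will be included in the efficiency analysis", and then "Non-compliance data will be analyzed by the instrumental variable".

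The outcome measures section sets the endpoint: "The primary outcome will be the change in the amount of urine leakage at week 6 from the baseline, measured by a 1-h pad test". That section and Table 1 place the pad test at baseline, week 2 and week 6. Neither makes the test conditional on having had treatment.

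**The concern.** The two groups named as sources of missing data are defined differently. Treated women belong only if no valid evaluation exists. Women who were never treated belong because they were never treated; nothing is said about whether they were measured.

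Under an all-randomized ITT population, a woman who has no sessions but does the week-6 pad test has a real outcome, and that outcome should be analysed. The printed rule sends her to imputation instead.

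If the rule is followed, few or no never-treated women supply observed outcomes, so an imputation model has to learn from treated women. If it does so within arm, a never-treated EA woman receives a treated EA outcome. The result then moves away from the effect of being assigned to EA and towards the effect in women who were treated, while still being called ITT.

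**Working it through.** **Inputs from the article.** Difference 1 g, SD 2.61 g, one-tailed 5%, power 90%, 117 per group, predicted drop-out 20%, final size 250 per group (sample size calculation); two-tailed 5% for the analysis (statistical analysis).

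**Inputs that are assumptions.** The never-treated share d is not in the article, so a range of 2% to 20% is shown, equal in both arms. The EA-minus-sham difference among never-treated women, r, is taken as 0 because they received neither procedure; r = 0.5 g is shown for sensitivity. The imputation is assumed to borrow from treated women of the same arm.

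**Step 1: the plan's own figure.** n = 2 × (1.645 + 1.282)² × 2.61² / 1² ≈ 116.7, so 117 per group. This reproduces. The concern disputes no stated figure; 1 g serves only as the scale.

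**Step 2: the two estimates.** The difference over all randomized women is (1-d) × 1 + d × r. Imputing never-treated women as treated returns 1 g. The overstatement is 1 / [(1-d) + d × r] - 1, which for r = 0 is 1/(1-d) - 1.

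| d | Women per arm (d × 250) | All-randomized difference, r = 0 | Overstatement, r = 0 | Overstatement, r = 0.5 g | Two-sided power, 250 per arm, r = 0 |
|---|---|---|---|---|---|
| 2% | 5 | 0.98 g | 2.0% | 1.0% | 0.987 |
| 5% | 12.5 | 0.95 g | 5.3% | 2.6% | 0.983 |
| 10% | 25 | 0.90 g | 11.1% | 5.3% | 0.971 |
| 20% (ceiling) | 50 | 0.80 g | 25.0% | 11.1% | 0.929 |

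The last row is a ceiling, not an expectation: 20% is the prediction for all drop-out, and never-starters are at most a part of it.

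**Step 3: check by simulation.** 250 per arm, SD 2.61 g, 4,000 runs. Untreated women were given a mean change of zero. The sham-arm change was 0.64 g, borrowed from the pilot's shallow-EA arm.

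- Effect 1 g, 10% untreated in both arms: 1.01 g imputed, 0.90 g measured.
- Effect 1 g, 20% in both arms: 1.00 g imputed, 0.80 g measured.
- Effect 1 g, 20% in EA and 10% in sham: 0.99 g imputed, 0.73 g measured (by arithmetic, 0.8 × 1.64 - 0.9 × 0.64 = 0.74 g).
- No effect, 10% in both arms: 0.00 g imputed, 0.00 g measured.
- No effect, 20% in EA and 10% in sham: 0.00 g imputed, -0.06 g measured.

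The rule enlarges a real effect. It does not produce one where none exists. The unequal-share cases are less relevant to never-starters: participants are blinded, so those who have had no session have little reason to differ by arm.

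**The case against.** The strongest reply is that item 4 is an analysis rule, not an instruction to sites. It can be read as saying only where absent values are expected to come from, with no intention of discarding a pad test that was done. The article is also condensed: withdrawal procedures may sit in the full protocol and the imputation model in an analysis plan that is not shown. Much of this stands. The missing model is no finding in itself, and the size of the bias can be shown only under an assumption about it. What does not fall away is the printed definition, which makes lack of treatment sufficient to count as missing.

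A reader might go further in four ways that the article does not support.

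- *Women who stop treatment are imputed too.* The sentence does not name them. A woman who starts, stops and has data comes under non-compliance, which is included and handled by instrumental variable. That method usually targets an effect of treatment received rather than the ITT effect, but it is not imputation.
- *Sites cease to assess women off treatment.* No sentence says so. The article neither promises nor forbids measuring them.
- *Leaving treatment and leaving assessment are one event.* Item 1 of the analysis says "The total drop-out rate and the drop-out rate due to adverse events, of both groups, will be compared using Fisher’s exact test", but it does not define drop-out as stopping treatment. Item 3 compares implementation of the intervention separately, and Table 1 has its own compliance row.
- *The effect would be overstated by 25%.* That needs all of the predicted 20% drop-out to be women with no EA effect who are imputed as treated. The rule reaches only never-starters.

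**Conclusion.** The point holds for women who never start treatment. Classing them as missing because they were untreated contradicts an ITT population of all randomized participants, when their week-6 outcome can be collected at a visit already scheduled.

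The likely size is modest: about 2% to 5% overstatement of a real effect at a 2% to 5% never-treated share, and 11% at 10%. These figures rest on within-arm borrowing from treated women, equal shares in the two arms and no specific EA effect in never-treated women. None of the three is stated in the article. A false positive is not at stake, since with no true effect the imputed difference stays at zero. Power is not at stake either: it remains at least 0.929 for the 1 g planning effect across the range shown. The change should still be made, because it replaces a printed rule that biases the ITT estimate, and no later analysis can recover a pad test that was not done.

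**What to change.** Replace the missing-data rule in item 4 with wording to this effect:

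- Every randomized woman, including those who never start or who stop treatment, is asked to do the scheduled week-6 1-h pad test and complete the scheduled diaries, unless she withdraws consent to follow-up.
- Observed values enter the ITT analysis whatever treatment was received.
- Only values actually absent are imputed, under a stated assumption.
- The instrumental-variable analysis of non-compliance is supplementary to the ITT result.

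For women who stop treatment, the first two items are clarification only.

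The cost is a change of wording and a note to sites. The visits are already in Table 1, and the article says that the trial is still recruiting, so the change can still affect data collection. The downside is some effort to bring back women who are off treatment, not all of whom will agree.
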